#### Data analytic plan

Basic data screening and descriptives will be conducted for all quantitative variables. We will explore and statistically adjust for baseline equivalence between conditions on all individual outcomes and all school, teacher, and student variables following established guidelines [83]. For all longitudinal modeling, the statistical adjustment will use baseline intercepts as random terms; for dissimilar outcome domains, non-equivalent baseline variables will be included as covariates. Data missing at random will be modeled using full information maximum likelihood estimation or multiple imputation as appropriate.

Unless otherwise indicated, quantitative analyses will employ mixed-effects models using time points nested within classrooms within the school. Standard model-building procedures will be used [84, 85]. Classroom and time trends will be allowed to randomly vary. Piecewise time models will estimate slopes from T1 to T4 (training), T5 through T6 (first month of post-training implementation), T7–T11 (first academic year), and T12–T13 (sustainment during the subsequent year). Variables for condition and condition x time will be added, and iterative models with possible control variables will be tested. Covariates not contributing at *p* < 0.10 based on likelihood ratio tests will be removed. Level 2 and 3 predictors will be fit and excluded for the same reasons. We will obtain estimates of whether there were statistically significant differences among the groups on the rate of change over time (i.e., slope) and whether there are statistically significant group differences in the average score on each outcome variable at the final timepoint of each piecewise segment. Models will be generalized, with appropriate link functions (e.g., log-link, Poisson) applied based on distributional form (e.g., dichotomous, zero-inflation). Estimation will be fit using full maximum likelihood. Models will be assessed for possible violations of assumptions. Goodness-of-fit will be evaluated using likelihood ratios, deviance statistics, and fit criteria. The inference will be evaluated relative to *p* < 0.05. For RQs with multiple DVs, we will adjust for the false discovery rate using Benjamini and Hochberg’s procedure [86].

We will use thegeneralizer.org to compare our sample to national demographics to examine the generalizability of our findings [58]. If not generalizable, we will use inverse probability weighting to increase the representativeness of estimates [87].*RQ 1a*: A series of 3-level piecewise mixed effects models will be used to test our primary hypotheses: (1) the BASIS-T condition will show steeper gains than the ACC condition from T1 to T2 (e.g., more favorable attitudes towards EBPPs, increased social norms; enhanced task and maintenance self-efficacy; stronger intentions to implement) and (2) both groups will decline after training (T3–T5) as has been found in past TPB research [88], and in the BASIS-T pilot trial [33], but the BASIS-T condition will have longer sustained between-condition effects after training from T3 to T13. Dependent variables will include subscale scores on attitudes, social norms, self-efficacy, intentions, and maintenance self-efficacy.*RQ 1b*: BASIS-T impact on behavioral implementation outcomes will be tested in two ways. First, a mixed effects model will examine whether the proportion of teachers in the BASIS-T condition who adopt PGD (i.e., initiate PGD) is higher than the proportion in the ACC condition. Second, Kaplan–Meier time-to-event analyses will be used to compare conditions on the number of days between training and PGD initiation. Reach will be analyzed using mixed effects models comparing BASIS-T vs. ACC on the proportion of students in each classroom (out of those eligible based on whether their classroom teacher participated in PGD training) who received PGD practices. Impact on PGD fidelity will be analyzed using mixed effects models with sessions within teachers, testing for the main effects of condition on adherence and participant responsiveness ratings derived from both PGD observational and self-report fidelity data. We will test the effects of BASIS-T on PGD sustainment and delayed implementation using the multilevel longitudinal analytic approach described for RQ1a.*RQ1c*: BASIS-T impact on student SEB and academic outcomes will be tested via mixed effects multilevel models as described in RQ1a, with academic data aggregated to the classroom level. Dependent variables will include post-intervention scores on teacher ratings of student behavior.*RQ2a*: Whether mechanisms of behavior change mediate the impact of BASIS-T on implementation outcomes will be analyzed using path analysis [89] extending traditional mediation modeling to a multi-level framework for nested data [90, 91].*RQ2b*: To test whether the effect of BASIS-T on implementation and student outcomes is moderated by teacher factors (e.g., demographics, baseline intentions to implement) and school-level factors, we will add moderators and interaction terms to the analytic approach described in RQs 1a-c.*RQ2c*: To explore what explains “residual” teachers whose implementation behaviors are not accounted for by the mediation model, we will analyze qualitative interviews with teachers who have a difference between predicted (based on BASIS-T putative mechanisms) and actual implementation behavior of ≥ 1 SD. Data will be coded using an integrated directed and conventional content analysis [92] approach as certain codes will be conceptualized during the interview guide development and driven by the exploration, preparation, implementation, sustainment [93] framework (i.e., deductive approach) which will allow for the examination of influences on implementation across multiple levels and phases. Other codes will be developed through a close reading of an initial subset of transcripts (i.e., inductive approach). These themes will provide a way of identifying and understanding the most salient factors that impact implementation and extend beyond the existing BASIS-T mechanisms and theory of change. After a stable set of codes is developed, a consensus process will be used in which all reviewers independently code and compare their coding to arrive at consensus judgments through open dialogue [78, 79, 94].*RQ2d*: We will process cost data by assigning monetary values to each cost. We will use CostOut [95], a web-based program for conducting cost-effectiveness analysis in education, to identify nationally representative unit prices for ingredients. For qualitative data, we will rapidly analyze responses on an ongoing basis [96, 97] and incorporate newly identified costs into future surveys for quantitative measurement.

Once cost data collection is complete, we will calculate the costs of BASIS-T versus PGD implementation-as-usual based on the unit price and amount of each cost category (e.g., hours spent, items purchased). We will use CostOut to standardize dollar values, including an index year for inflation; cost-of-living adjustments; and discounting costs from different years to account for preferencing of delayed over immediate costs [80, 95]. We will generate descriptive statistics describing typical costs (i.e., means, standard deviations) for each condition and incremental costs of BASIS-T over implementation as usual.

Once the cost analysis is complete, we will use CostOut to calculate the cost-effectiveness [81] of BASIS-T versus PGD implementation as usual. This will involve calculating a series of incremental cost-effectiveness ratios for each implementation and student outcome measure, representing the incremental costs of BASIS-T divided by its incremental benefit (i.e., effect size). Themes about BASIS-T mechanisms and outcomes from the qualitative teacher interviews will allow for mixed-method cost-effectiveness evaluation [82] in which participants’ views help determine whether the results were worth the cost. For both cost and cost-effectiveness analyses, we will conduct sensitivity analyses that vary key sources of uncertainty in the models to examine the robustness of our estimates [98, 99].

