### Randomization

This study will employ a randomized cluster-blocked cohort design with random assignment at the school level to eliminate the possibility of condition contamination among teachers. Schools will be blocked within the district by a number of teachers participating in the study, school enrollment, % of non-White students, % of students who qualify for free/reduced lunch, and mean teacher baseline BASIS-T mechanisms of change (e.g., self-efficacy). These variables were chosen because they are associated with EBPP use and student academic outcomes [59]. We will create matched pairs using the nearest neighbor approach [60] and randomly assign schools within pairs to condition. Randomization will occur to the greatest extent possible, although there may be some situations where trainers in only one condition are available when school staff are available to be trained; these situations will be considered essentially random. School personnel and participants will be masked to condition.

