#### Power

Our planned sample, including attrition, will provide sufficient power to test linear effects on teacher- and classroom school-level variables with a minimum detectable effect size (MDES) of small to medium effects, *d* = 0.37. We used PowerUp! [100] assuming clustering, final samples of 46 schools evenly randomized to condition, 6 teachers per school (after 15% attrition), school ICCs of 0.10 (consistent with our pilot data), and 13 timepoints. With the same assumptions as above, plus an assumption that 50% of the schools will be in a given moderator subgroup, our MDES for detecting any single school-level moderator variable is 0.48 and teacher-level moderator variable is 0.45. For mediator analyses, PowerUp! identifies power using the Sobel test, joint test, and Monte Carlo simulations. Across all tests, we will have a power of greater than 0.80 to detect reasonable and likely effects, based on our pilot trial and standard interpretations of effect sizes. We will detect an MDES equivalent to Cohen’s *d* = 0.60 for the treatment-mediator pathways (e.g., BASIS-T to implementation intention) which is lower than our actual obtained effect size from the pilot trial (which ranged from *d* = 0.61 to 1.16 for our primary mediators), an MDES of Pearson’s *r* = 0.3 for the mediator-outcome path (e.g., implementation intention to student behavior, a small effect), and an MDES of *d* = 0.10 for the direct path from treatment to student outcome.

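### Final models fitted by full maximum likelihood with 46 randomised schools make school-level condition tests somewhat too liberal; refit continuous outcomes by REML with small-sample degrees of freedom

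*Protocol article*

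**What the plan says.** The Data analytic plan sets the estimator for the mixed models: "Estimation will be fit using full maximum likelihood". It then says "The inference will be evaluated relative to *p* < 0.05". It names no REML refit, degrees-of-freedom method or other small-sample correction.

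The models have three levels: occasions, classrooms and schools. School-level terms can enter in two ways. Baseline variables found to differ between conditions may be added as covariates, and the model-building step tests further predictors. On selection it says "Covariates not contributing at *p* < 0.10 based on likelihood ratio tests will be removed" and "Level 2 and 3 predictors will be fit and excluded for the same reasons".

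Condition is a school-level factor: the Randomization section describes "random assignment at the school level to eliminate the possibility of condition contamination among teachers". Five matching variables are listed there, and the method is "We will create matched pairs using the nearest neighbor approach [60] and randomly assign schools within pairs to condition". No pair term, fixed or random, appears in the stated model. The Power section assumes "final samples of 46 schools evenly randomized to condition, 6 teachers per school (after 15% attrition), school ICCs of 0.10".

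**The concern.** Full ML estimates a variance as if the fixed effects were known. At school level it divides the between-school sum of squares by 46, not by 46 minus the number of school-level fixed effects. The school variance is biased low, and so is the standard error of any contrast that rests on it. Each retained school covariate widens the gap.

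ML is needed to compare models with different fixed effects by likelihood ratio, which is how the plan builds its models. It is not needed for the final estimates and p-values of continuous outcomes. The planned Benjamini-Hochberg adjustment does not help, because it takes the p-values as valid.

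At stake is a nominal 5% test that runs at roughly 5.5 to 7.6% for the affected contrasts.

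**Working it through.** **Inputs.** From the Power section: J = 46 schools, n = 6 teachers per school, school ICC 0.10. From the Data analytic plan: full ML, alpha 0.05 (taken as two-sided, since sidedness is not stated). The number of school covariates finally retained is not given. Five is used as the main case because five matching variables are listed; 0, 3 and 8 show the range.

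**The plan's own figures.** The only error rate stated is the nominal 5%. The one computed figure on these inputs is the MDES of d = 0.37. A two-level, two-sided calculation at 80% power gives (2.015 + 0.850) × √[4 × (0.10/46 + 0.90/276)] = 0.42. A value of 0.37 arises one-sided (0.373), or in a three-level model with 13 time points if the teacher-level variance share is about 0.52. Neither condition is stated, so 0.37 can be neither confirmed nor called wrong. Nothing below depends on it.

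**Closed form.** Take a balanced random-intercept model with p school-level fixed effects (intercept, condition, covariates) and a school variance not estimated at zero:

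- SE(ML) / SE(REML) = √[(46 − p)/46]
- True rejection rate = 2 × P(T with 46 − p df > c × that ratio), where c = 1.96 for Wald z or the t quantile for a t reference

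Condition only (p = 2): ratio √(44/46) = 0.978, giving 6.2% (z) and 5.5% (t).

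Five covariates (p = 7): ratio √(39/46) = 0.921, giving 7.9% (z) and 7.0% (t).

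**Simulation.** 100,000 null trials per setting, with exact ML and REML solutions, zero-variance estimates allowed, ICC 0.10 and no within-pair correlation:

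| School covariates | ML, Wald z | ML, likelihood ratio | ML, t | REML, z | REML, t | Mean ML school variance / truth |
|---|---|---|---|---|---|---|
| 0 | 6.2% | 5.7% | 5.5% | 5.6% | 4.95% | 90% |
| 3 | 7.0% | 6.4% | 6.2% | 5.6% | 4.94% | 74% |
| 5 | 7.6% | 7.1% | 6.8% | 5.7% | 4.94% | 64% |
| 8 | 8.7% | 8.2% | 7.7% | 5.7% | 4.94% | 49% |

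A separate run gave 6.7% for the ML t test with five covariates. Over ICC 0.05 to 0.30, ML with Wald z ranges from 5.9 to 6.2% with condition only and from 7.6 to 9.2% with eight covariates.

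**How much is due to ML.** With condition only, REML with z already gives 5.6%, so about half of the 1.2-point Wald z excess comes from the normal reference. With five covariates, moving from REML to ML on the z reference adds about 2.0 points (5.7% to 7.6%, before rounding). The reference distribution adds about 0.7 (4.94% to 5.7%).

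**Effect of the p < 0.10 rule.** With five candidate school covariates and backward likelihood-ratio elimination (5,000 runs), 0.6 covariates are kept on average if none has a true effect, and 2.2 if together they explain half the school variance. Type I error is then 6.8 to 7.2% (ML, z), 6.0 to 6.4% (ML, t) and 5.3 to 5.6% (REML, t). On the same t reference, ML accounts for about 0.7 to 0.9 points.

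**Effect of matching with no pair term.** Condition only, 40,000 runs. The share of school variance common to a pair is an assumption; the protocol gives none.

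| Shared within pair | ML, z | ML, t |
|---|---|---|
| 0 | 6.1% | 5.4% |
| 25% | 4.8% | 4.3% |
| 50% | 3.8% | 3.3% |

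**Condition by time.** If slopes vary only among teachers, the relevant count is 276. With two fixed effects the ratio is √(274/276) = 0.996, so the bias is negligible. If a school-level random slope is fitted, the school-level result applies.

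**The case against.** The strongest reply is that the problem may be absent in practice. Schools are matched on variables chosen for their association with the outcomes, so some within-pair correlation is expected. A model that leaves pairs out is then conservative: at a 25% share the ML test is already at or below 5%. REML with t would give 3.9% at 25% and 3.0% at 50%, further from nominal. This is correct and limits the claim. It does not justify the estimator: the offset depends on an unknown matching benefit, and two errors of unknown size need not cancel.

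Second, the primary RQ 1a hypotheses largely concern slopes, and no school-level random slope is named. For those tests the bias may be negligible. It remains for the group differences at the end of each segment, which the plan also tests.

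Third, binary adoption, reach, Kaplan-Meier times and path-analysis mediation lie outside the ordinary REML argument. That stands. The article also does not forbid a REML refit, and degrees-of-freedom methods are often left to an analysis plan. But the estimator is stated here, and a reader following the text would use it for the final p-values.

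A reader might infer two stronger things. One is that false positives would more than double, to about 11 to 13%. That figure (13.3% with z, 11.1% with t) arises only if the 23 pairs are fitted as fixed effects under full ML. The protocol states no pair term, and a random pair effect would not cost 22 degrees of freedom. The other is that every linear condition comparison exceeds 5%. The matching and slope results above show that it need not.

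**Conclusion.** The point holds in a limited form. The stated estimator understates school-level variance, and condition contrasts resting on that variance are somewhat too liberal. The size is about 0.5 to 1.2 percentage points above 5% with condition alone, and about 1.7 to 2.6 points if five school covariates are retained. It is less if the p < 0.10 rule drops most of them.

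These figures assume a two-level balanced model, complete data, ICC 0.10, two-sided tests and no within-pair correlation. They were not derived for the full three-level piecewise model. This is a minor technical improvement. It does not show that the trial's conclusions would be unsound.

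**What to change.** Keep full ML for likelihood-ratio comparisons of fixed effects. State that final models for continuous outcomes are refitted by REML, with Kenward-Roger or Satterthwaite degrees of freedom for condition and condition by time. For non-Gaussian mixed models, refer the condition test to a t distribution with schools minus school-level parameters as degrees of freedom. This corrects the reference distribution there, but not the variance bias itself.

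The protocol should also say whether pairs enter the model. If they are fitted as fixed effects, REML with t holds the error at 4.8% in the same simulation; leaving an effective pairing out keeps the test conservative under either estimator.

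The cost is one sentence, a software option and wider intervals. Against ML with Wald z, the interval widens by a factor of (2.015/1.960)/0.978 = 1.05 with condition only and (2.023/1.960)/0.921 = 1.12 with five covariates. REML is also likelihood-based, so the handling of outcomes missing at random is kept.

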### Participants and recruitment

Teachers from schools in the USA will be recruited to participate. Inclusion criteria include being a teacher at an elementary (typically K–5th grade or K–8th) school and not having been trained or supervised in delivering PGD in the past 5 years. We will recruit approximately 276 teachers from 46 elementary schools in the USA. The final balance of teachers and schools is dependent on recruitment, with the goal of meeting minimum statistical power. Schools will be approached to participate via multiple routes, including leveraging existing relationships and networks, educational listservs, and posting on social media. Interested school representatives may respond using the interest survey linked in flyers or by contacting the research team via email. The generalizer (generalizer.org), a free, web-based tool for selecting schools for randomized controlled designs that are statistically representative of a chosen inference population, will also be used to help assure the representativeness of our sample [58]. Strata will be created on urbanicity, school race/ethnicity, school percent female, school percent free and reduced lunch, school size, school percentage English language learners, and the number of schools in the district.

Once schools have been selected, teacher recruitment will proceed for both cohorts of schools with the assistance of site administrators. Principals will provide us with the email addresses of teachers in their schools. Research staff or school leadership will contact eligible participants by email or phone to describe the purpose of the study, research procedures, and incentives. Informed consent will be collected online prior to training (Additional file 3) and teachers will be free to decline participation. Monetary incentives will be provided to participating teachers and schools.

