#### Quantitative surveys

Participants will complete secure web-based surveys at 13 timepoints spanning three phases: preparation (times 1–4), active implementation (times 5–11), and sustainment (times 12–13 follow-up during the next academic year) [45]. Time 1 will occur during informed consent, time 2 in the days immediately before BASIS-T/ACC pre-training, time 3 immediately after pre-training, time 4 immediately after post-training, time 5 two weeks after training, time 6 four weeks after training, times 7–11 monthly until the end of the academic year, time 12 at the beginning of the subsequent academic year, and time 13 during the spring of that academic year. Teachers will self-report demographics, perceptions about BASIS-T (when relevant) and PGD training, BASIS-T mechanisms, implementation outcomes, organizational moderators (implementation climate, leadership), and time and resources used for PGD implementation. From times 7–11, to reduce the respondent burden we will use a random item planned missingness design for measures of attitudes (1 item selected per subscale), action self-efficacy (2 items selected), and subjective norms (1 item selected per each scale).

Data collection regarding students will focus on classroom behavior, behavioral discipline, attendance, and academic performance and will be collected in aggregate at the classroom level, without individual identifiers. Teachers will complete the first secure online survey on student classroom behavior at time 4, as earlier data collection would prohibit teachers from having an adequate sample of student behavior. At the end of each school year, academic and behavioral data (attendance, disciplinary actions, grades, and standardized test scores) will be requested for all students who were in classrooms of participating teachers; these data will be obtained in aggregate at the classroom level and no individual identifiers will be provided to the research team.

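### Primary hypothesis 1 of RQ 1a is placed on T1 to T2, two surveys that both precede any session, and neither RQ 1a window matches the model's T1–T4 training piece

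*Protocol article*

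**What the plan says.** Three places in the protocol article bear on this.

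- **Quantitative surveys** fixes the schedule. "Time 1 will occur during informed consent", followed by "time 2 in the days immediately before BASIS-T/ACC pre-training, time 3 immediately after pre-training, time 4 immediately after post-training". Participants and recruitment adds that "Informed consent will be collected online prior to training".
- **Data analytic plan, RQ 1a**, gives two hypotheses that it labels primary. The first is that "the BASIS-T condition will show steeper gains than the ACC condition from T1 to T2", and its examples cover attitudes, norms, task and maintenance self-efficacy, and intentions. The second is that "both groups will decline after training (T3–T5"), with between-arm effects lasting longer for BASIS-T from T3 to T13.
- **Data analytic plan, general model**: "Piecewise time models will estimate slopes from T1 to T4 (training), T5 through T6 (first month of post-training implementation"), then T7–T11 and T12–T13. The arms are to be compared on slopes and on mean scores at the last survey of each segment.

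BASIS-T structure describes two 75-minute sessions, one before and one after PGD training. The first addresses attitudes, norms and perceived control. The second is for action planning and problem-solving planning, which Table 1 links to maintenance self-efficacy.

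**The concern.** A primary hypothesis about the effect of a strategy has to span at least one delivery of that strategy. T1 to T2 spans none. Run literally, the test compares drift between two baseline surveys, and a null result would say nothing about BASIS-T.

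Hypothesis 2 has a related fault. Its window for decline after training opens at T3, when teachers have had only the pre-training session. For maintenance self-efficacy, T3 to T4 contains the session meant to raise it, yet the hypothesis predicts decline there.

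The model segments match neither window, so the article does not settle which contrast is the primary test. An analyst who saw the problem would have to choose among T1–T3, T2–T3, T2–T4 and T1–T4, for several mechanism scales, possibly with data in hand.

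**Working it through.** **Step 1. Order of events** (Quantitative surveys; BASIS-T structure).

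| Event | Received by then |
|---|---|
| T1, at consent | nothing |
| T2, days before pre-training | nothing |
| Pre-training session, then T3 | motivational session (BASIS-T) or control session |
| PGD training, post-training session, then T4 | both sessions and PGD training |
| T5, two weeks after training | as at T4 |

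T3 is the first survey at which the arms can differ because of a session. T4 is the first at which training is complete.

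**Step 2. Expected T1–T2 contrast.** Let the effect be 0 at T1 and T2 and d from T3. The expected between-arm difference in change is (0 − 0) for T1–T2, and (d − 0) for T2–T3 and for T2–T4 if the effect holds. Randomization says that school personnel and participants are masked, so the article gives no reason to expect an anticipation effect that differs by arm.

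**Step 3. Rejection rates.** The protocol gives no figure for this test, so there is none to reproduce. Inputs from Power: 46 schools split evenly, 6 teachers each, school ICC 0.10, MDES 0.37 and pilot effects of 0.61 to 1.16. Alpha is 0.05 (Data analytic plan), taken here as two-sided. Assumed, not in the article: teacher variance share 0.5, residual share 0.4, equally spaced waves, and a step effect that starts at T3 and holds at T4. The test is a t-test on school means of change, with 4,000 simulated trials per scenario.

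| True d | T1–T2 | T2–T3 | T2–T4 | T1–T4 slope |
|---|---|---|---|---|
| 0 | 0.054 | 0.055 | 0.045 | 0.048 |
| 0.37 | 0.052 | 0.917 | 0.928 | 0.985 |
| 0.61 | 0.048 | 1.00 | 1.00 | 1.00 |
| 1.16 | 0.046 | 1.00 | 1.00 | 1.00 |

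The simulation error around 0.05 is √(0.05 × 0.95 / 4000) = 0.0034, so every T1–T2 entry is within about 0.004 of 0.05, close to one standard error.

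Hand check at d = 0.37: a two-survey change averaged over 6 teachers has variance 2 × 0.4 / 6 = 0.133. The standard error between 23 and 23 schools is √(0.133 × 2/23) = 0.108, and 0.37 / 0.108 = 3.4. Against a critical value of about 2.0 this gives power near 0.92, as simulated. For T1–T2 the numerator is 0.

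**Step 4. Hypothesis windows against model segments.** Hypothesis 1 needs T1–T2, and hypothesis 2 needs T3–T5 and T3–T13. The segments are T1–T4, T5–T6, T7–T11 and T12–T13. None coincides with a hypothesis window.

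**The case against.** The strongest reply is that a literal T1–T2 contrast is not in the planned model. RQ 1a is to be tested with piecewise models whose first piece runs from T1 to T4, and the arms are also to be compared at T4, after both sessions. This stands. Under the assumptions above, the T1–T4 slope has power 0.985 at d = 0.37, above either two-survey change. A reader might infer that the trial cannot detect an effect on the mechanisms; the article does not support that.

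A reader might also infer that a single T1–T4 line misstates the training effect by a known amount. For a noiseless step from 0 to D after T2, a least-squares line gives 1.1D at T4 with equally spaced waves. With assumed survey days (T1 30 to 60 days and T2 2 days before pre-training, T4 7 days after) it gives 0.75D to 0.82D. The direction depends on a time coding that the article does not state, the days are assumed, and the planned model is a mixed model with further pieces. No bias figure can be claimed.

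Nor is it an established fault that intervals such as T4–T5 or T11–T12 lie in no listed piece. The list may be shorthand for the study phases, and how segments join is commonly left to the full plan.

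The time labels may come from a different numbering of surveys. The article does not say so, and these are specific statements that conflict with its own schedule, not details left for later.

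**Conclusion.** The concern holds as a contradiction in the stated primary hypotheses. On T1–T2 the expected between-arm difference is zero, and the rejection rate is 5% for any true effect, including the largest pilot effect of 1.16. This needs only the published schedule, assignment that is random or effectively so, and no anticipation effect that differs by arm. It does not depend on the variance split. The powers quoted for the other windows do.

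Hypothesis 2 starts its post-training window one survey too early, and neither hypothesis matches a model segment. The consequence is a primary hypothesis that is uninformative as written and an unsettled choice of window. It is not a design without power: the T1–T4 piece and the T4 comparison can detect an effect.

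**What to change.** Reconcile Quantitative surveys, the general model in Data analytic plan and the RQ 1a paragraph before analysis.

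- **Hypothesis 1**: the between-arm difference in change from the pre-session surveys (T1/T2) to the first survey after the relevant session. That is T3 for attitudes, norms, task self-efficacy and intentions, and T4 for maintenance self-efficacy. Check first that each scale is collected at those surveys; the article refers the detail of its measures to Additional file 4, which is not shown here.
- **Hypothesis 2**: change from T4 onward.
- **Time coding**: estimate these contrasts directly, for example with survey wave as a categorical factor over T1–T4, or with knots at T2 and T3, and with no arm difference in slope before T2. A single T2–T4 piece without a knot at T3 would not do. For the same step effect, with the T1–T2 piece common to both arms, put the time since T2 at x = (0, 0, 1, 2) and the differences at (0, 0, D, D). The slope is 1.5D / 2.75 = 0.55D, so only 0.55D is recovered at T3. With the assumed days, x = (0, 0, 2, 9), the slope is 5.5D / 54.75 = 0.10D per day, or 0.20D at T3.
- **Sustainment**: keep the separate T12–T13 piece, because RQ 1b reuses the RQ 1a approach for PGD sustainment.

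The cost is wording and time coding, with slightly more parameters. Knots at T2 and T3 with no arm difference before T2 need two arm-by-time terms in the training phase instead of one. If the scales are measured at the surveys named, no new data are needed.
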